## DURATION OF THE TRIAL / STUDY AND PARTICIPANT INVOLVEMENT

The project will take place over 2 years with recruitment for the study proposed to begin 3 months after the study commences i.e. April 2012 and continue for 18 months.

Within 5-30 days of identification of potentially eligible participants, the participant will enter a screening phase. The purpose of the 5–30 day screening phase is to determine if the individual post-stroke is willing to participate in the trial and meets preliminary inclusion and exclusion criteria for study participation. If the participant voluntarily provides informed consent and successfully completes all physical and cognitive screens performed in the screening phase, the participant's treating physician will be asked to review the inclusion and exclusion criteria and provide a letter of support for inclusion in the study.

Participants meeting inclusion criteria will be referred for baseline assessment by the independent assessor and asked to give informed consent, after which randomisation will occur and study enrollment will begin.

During the active treatment period, participants will attend the outpatient rehabilitation setting for 1hr., three times weekly for 8 weeks. Participants will then be assessed at follow up 3 months after baseline and study enrolment ceases.

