| Description of interventions | Overground and treadmill Visual cue treatment groups: 1hour session 2X/week for 8 weeks, 6 treating centres: Moseley Hall Hospital, Birmingham Heartlands Hospital, Sandwell Hospital, Rowley Regis Hospital and,  Control group: usual caregait training of the same intensity/frequency and duration provided at the same centres. |
| Duration of study | Planned start date April 2012 – 24 months duration, 3 months per participant. |
| Randomisation and blinding | Randomisation will be by central telephone allocation from University of Nottingham Clinical Trials Unit. Potential participants will be identified by clinicians of rehabilitation team in outpatient neuro-rehabilitation clincis to which they are referred. Informed consent will be obtained from those meeting inclusion criteria who will then be referred for baseline assessment, after which randomisation will occur. The independent assessor will be blinded to treatment allocation. The assessor will record a guess of participants’ group allocation for later examination of the success of masking. Block randomisation will be used to stratify participants into two groups according to gait speed (Severe group: <0.4 m/s; Moderate group: between 0.4 m/s and 0.8 m/s) to obtain balanced groups on severity. |

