### Expected duration of participant participation

During the active treatment period, participants will attend the outpatient rehabilitation setting for 1hr., two times weekly for 8 weeks. Participants will then be assessed at follow up 3 months after baseline.

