**Potentially Eligible Participants Identified**

**Standard care: 1hr, 3X weekly for 8 weeks**

**VCT intervention: 1hr, 3X weekly for 8 weeks**

**Post-treatment assessment**

**Post-treatment assessment**

**Three month assessment**

**Three month assessment**

**Figure 1: Flow diagram of trial conduct**

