**Visual Cue Training (VCT):**

Feasibility of VCT delivered in two ways will be examined. Both overground VCT and treadmill based VCT will share the same frequency, duration, intensity and progression as per below. Only the content of VCT will differ slightly between the two VCT arms and is detailed below.

Frequency: 2X/week, 8 weeks

Duration: 1hr,consisting of: warm up – 5 minutes, stretching – 5 minutes, Set up for training programme – 5 mins, training programme – 20-30 minutes overground walking practice (+ 10 minutes for rests as required) and cool-down - 5 mins

Intensity: The training program will begin with 5 minute bouts of walking with VCT interspersed with rests to total 20-30 minutes of walking practice. Once this is achieved, then the number of bouts may be decreased and the length of each bout increased. The target exercise capacity is 20 minutes of continuous, independent, good stepping. Good stepping is defined as walking with (1) an upright trunk with pelvic rotation to achieve limb loading, (2) symmetrical stride length, (3) symmetrical swing and stance time, (4) hip and knee flexion moments during swing initiation and swing, and (5) hip and knee extensor moments during stance and push-off with proper stance and swing kinematics.

In order to contrast intensity between VCT and UC groups a pedometer will be worn during training sessions to record the number of steps taken in each condition.

During the 20–30 minute training sessions the Borg scale Rate of Perceived Exertion will be monitored every 10 minutes initially to assure that the intensity of walking practice remains within acceptable limits. The American College of Sports Medicine criteria for terminating an in-patient exercise session are followed according to guidelines shown to be effective for persons post-stroke with multiple comorbidities([Rimmer 2000](#_ENREF_38)) and described in “stopping rules and discontinuation” above.

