One treatment site will deliver VCT on a force-instrumented treadmill (CMill, Forcelink, NL) which uses assessment of each footfall to determine the timing and location of visual cues projected as light targets shone 2-3 steps ahead on the treadmill. stepping stones (dimensions: shoe length by 30cm in width) will be projected on the treadmill, such that the current and upcoming (approximately 2 steps ahead) stepping stones will be visible to the patient (Figure 1). The stepping stones will be presented to the left and right to cue spatial and temporal requirements of left and right footfalls, respectively. Custom-made software for presentation of visual cues contingent upon measures of the ongoing gait cycle will be used to control the temporal and spatial specifications of the stepping stones. For example, if steps on the paretic leg are shorter than the non-paretic side (as measured by the instrumented walkway patients are traversing) then the light control system will present the subsequent paretic leg stepping stone (i.e. the next stride or 2 steps ahead) at a distance 10% further than the previous step (in accordance with the goal to improve spatial symmetry by 10%). Stepping stones will appear at the time patients need to initiate stance phase on the subsequent step. Participants will aim to walk for 5 minute bouts of continuous walking as tolerated as above and aim to increase to 20 mins of continuous walking. .

*Overground VCT:*

In the sites delivering overground VCT, participants will walk over a carpet walkway marked with the outline of a grid. The visual cues will take the form of red target stickers placed into appropriate grid boxes to denote target footfall locations according to the goal for changes in step lengths and widths. Initially, an assessment of spatial parameters of overground gait will be required in order to determine required locations of targets on the walkway grid.

Initially, participants will walk at their self-selected speed for 5 mins. Gait parameters of the participant will be assessed using the GAITRite system (CIR Systems Inc.), including step length, stride length, velocity, temporal and spatial symmetry and cadence. This will determine the participant’s starting target step lengths and target timing of their steps during the subsequent visual cue training.

*Both Overground and Treadmill VCT:*

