**Usual care:**

The purposes of the usual care (UC) group are to provide (1) a task specific-based intervention that does not include use of visual cues to influence quality or adaptability of gait (2) an equal number of interactions and time spent with a physical therapist to minimize any potential for bias due to differential exposure and minimize the risk for differential loss to follow-up, and (3) a credible training program so that the participants would consider themselves involved in meaningful therapy activity.

Frequency and Duration: To match the VCT group, the UC group attends 16 therapy visits (2 times per week for 8 weeks) with length of control and VCT group training sessions the same. In these ways, the UC intervention will plausibly control for Hawthorne effect but exclusively through interventions that do not include visual cues.

Intensity: The intensity of exercise in the usual care group will be matched to the VCT group. The target exercise capacity is 20 minutes of continuous, independent, good stepping (as defined previously). In order to contrast intensity between VCT and UC groups a pedometer will be worn during training sessions to record the number of steps taken in each condition.

Goal setting and progression:

Participants may be asked to identify their primary walking goal, i.e. "I want to walk my dog in the park", "I want to be able to walk on busy walkways e.g. busy shopping centres". At each training session, specific training goals are reviewed with the participant and in the context of achieving the participant's goal. As the participant's skills progress during the training, the therapists also ask the participant, "what is limiting you from achieving your goal relative to walking?". Therapists may use the response to tailor the goals and parameters of the training session.

Content:

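### The duration section and Figure 1 give three sessions a week (24 in all), while the synopsis, both regimen sections and Table 2 give two (16)

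*Protocol*

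**What the plan says.** Two places in the protocol give three sessions a week:

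- The section on the duration of the trial and participant involvement: "participants will attend the outpatient rehabilitation setting for 1hr., three times weekly for 8 weeks".
- Figure 1, in both treatment boxes: "Standard care: 1hr, 3X weekly for 8 weeks" and "VCT intervention: 1hr, 3X weekly for 8 weeks".

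Four places give two sessions a week:

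- The synopsis, for both VCT groups: "1hour session 2X/week for 8 weeks". The control group is to train at the same frequency.
- The section on expected duration of participant participation: "participants will attend the outpatient rehabilitation setting for 1hr., two times weekly for 8 weeks".
- The VCT regimen, which covers overground and treadmill delivery: "Frequency: 2X/week, 8 weeks".
- The usual-care regimen, which also states the total: "the UC group attends 16 therapy visits (2 times per week for 8 weeks".

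Table 2 gives no weekly frequency, but it numbers the sessions of the VCT programme: phase I is 1–4, phase II is 5–10 and phase III is 11–16. Nothing follows session 16.

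**The concern.** Session frequency is the dose of the intervention. The protocol fixes it at two values for the same participants over the same eight weeks. The sentences in the two duration sections are almost identical and differ in the number of weekly sessions. The higher figure cannot belong to one arm or one period, because the duration section applies it to all participants and Figure 1 applies it to both VCT and standard care. The document has no amendment log that marks either figure as superseded.

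Three things are at stake:

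- **Dose.** The duration section and the flow diagram are natural places for a site to look when booking visits. A site that followed them would book half as many sessions again as the regimen sections require. If sites read the document differently, dose varies between sites. The treadmill arm is the most exposed, because "One treatment site will deliver VCT on a force-instrumented treadmill" and a misreading there would reach that whole arm.
- **Matched contact.** The usual-care section relies on equal numbers of therapist contacts to limit bias. That holds only if every site works to the same number.
- **Attendance.** Compliance is measured by sessions attended and minutes delivered. Attendance expressed against plan needs one planned number.

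**Working it through.** **Inputs.** Treatment lasts 8 weeks in every statement. The frequency is 2 or 3 a week, as listed above. The stated total is 16 visits (usual-care regimen). The phase limits come from Table 2. The planned sample is 60, 20 per arm (synopsis; the randomisation section also gives 60). Training time is 20–30 minutes per session (VCT regimen).

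**Reproducing the stated total.** Sessions = weekly frequency × weeks.

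- Two a week: 2 × 8 = 16. This reproduces the stated 16 visits.
- Three a week: 3 × 8 = 24. This does not.

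**Check against Table 2.** The phases contain 4 + 6 + 6 = 16 sessions, and 16 / 8 = 2 a week. This source does not depend on any stated weekly frequency, and it supports two.

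**What three a week would do to Table 2.** Session 16 falls in week 16 / 2 = 8 at two a week. At three a week, 16 / 3 = 5.33, so it falls in week 6. Sessions 17–24 would then have no phase: 8 of 24, or one third. This applies to the VCT arms, since Table 2 does not cover usual care.

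**Size of the discrepancy.**

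| Planned quantity | Two a week | Three a week | Difference |
|---|---|---|---|
| Sessions per participant | 16 | 24 | 8 (8 / 16 = 50%) |
| VCT training time per participant | 16 × 20 / 60 = 5.3 h to 16 × 30 / 60 = 8 h | 24 × 20 / 60 = 8 h to 24 × 30 / 60 = 12 h | 2.7 to 4 h |
| Sessions per arm of 20 | 20 × 16 = 320 | 20 × 24 = 480 | 160 |
| Sessions for 60 participants | 60 × 16 = 960 | 60 × 24 = 1,440 | 480 |

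The sample size section gives 50 participants rather than 60. On that figure the totals are 50 × 16 = 800 and 50 × 24 = 1,200. The difference per participant and the 50% do not change.

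**Effect on attendance.** A participant who attends 16 sessions has attended 16 / 16 = 100% of plan at two a week, but 16 / 24 = 67% at three.

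**The case against.** The strongest reply is that the intended dose is not really in doubt. The VCT and usual-care sections are where the regimen is properly set out, and both say two a week. One gives the total, and Table 2 confirms it. The duration section is an overview, and Figure 1 is a schematic that shows two treatment streams in a three-arm trial. This is a fair account of which value is right, and it is why the correction goes to two. It does not make the other two places harmless, because they are current protocol text that states a dose and a site should not have to infer which one applies.

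A second reply is that the trial has controls that could catch a wrong schedule: a training day, manuals for both interventions, weekly calls, regular site visits, treatment logs and video checks in weeks 2 and 6. These reduce the risk. They do not remove it, and the manuals are not available here to show which frequency they give. The video checks carry little weight either way, since they count weeks of each therapist's first treatment period, which need not match a participant's own weeks.

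A third reply is that usual care is given at the same centres and by the same therapists, so a misreading at the treadmill site could also affect control participants there. This is true, but the treadmill arm would still be affected as a whole, while the other arms would be affected only in part.

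Some limits on the consequences also stand. No single statement gives the arms different frequencies. The sample size does not depend on the number of sessions. Costs are built from recorded therapist time. The drop-out endpoint is a count of participants who do not complete treatment, with no session threshold stated, so it is not directly altered. Attendance against plan is what changes.

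**Conclusion.** The contradiction is real, and the document itself shows which value is wrong. Two a week for 8 weeks gives 16 sessions, which matches the stated number of visits and the Table 2 phases. Three a week gives 24 and matches neither. The duration section and both Figure 1 boxes overstate the planned dose by 8 sessions per participant (50%), and in the VCT arms one third of a 24-session course would have no defined content.

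These are planned figures; what is delivered depends on attendance and on which statement each site follows. The trial-wide totals assume 60 participants. The error should be corrected because it concerns the dose of the intervention in current protocol text, but it does not threaten the design or the planned analysis.

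**What to change.** In the section on the duration of the trial and participant involvement, change the frequency to two times weekly. In both Figure 1 treatment boxes, change 3X to 2X. State once, for all three arms, that 16 sessions are planned, and use 16 as the denominator wherever attendance or completion is expressed against plan. Tell the sites about the correction and confirm that the treatment and participant manuals give the same number.

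The cost is three text edits, one added statement and a note to sites. Design, sample size and analysis are unchanged.

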### End of the Trial

The trial will be completed on the last treatment visit for the last recruited participant.

## SELECTION AND WITHDRAWAL OF PARTICIPANTS

### Recruitment

Recruitment and screening will be assisted via adoption into the Stroke Research Network portfolio – both the West Midlands and North West SRN managers have confirmed that they have the capacity to and will support recruitment and screening. Prior to recruitment we will meet with the local SRN teams and discuss the project and participant inclusion criteria.

Potential participants will be identified by hospital physiotherapy teams/Research Network nurses while in hospital at the time of acute admission. These patients will then be followed up at 6 months after stroke to determine willingness and eligibility to participate. Potential participants will also be identified by therapists at participating outpatient rehabilitation centres when patients are referred for treatment at each site. Identified participants will be screened consecutively.

Finally, we will also identify potential participants from individuals who have previously participated in studies at the Universities of Birmingham and Salford and who have agreed to be contacted about additional studies. These individuals will be identified by a member of the senior research team and, if necessary, a GP referral for treatment at a participating NHS site will be requested in order to enrol them in the study and provide treatment within the NHS.

Aphasic subjects can and will be included because usual carewalking training can be delivered to aphasic patients via the use of communication other than spoken language (e.g, gestures) and because the VCT training relies on visual cues rather than language ability. We will seek additional advice from CONNECT on how therapy interventions and outcome measures may be used with aphasic participants.

Most stroke survivors will recieve rehabilitation input from outpatient clinics longer than 6 months post-stroke. The trial will take place in outpatient rehabilitation clinics in West Midlands hopsitals. The proposed collaborating outpatient clinics include:

Birmingham Community Healthcare NHS Trust

R&D: Consortium RM&G Office ([[contact]](mailto:[contact]); [name])

Moor Green Outpatient Brain Injury Rehabilitation Service – [name]

Moseley Hall Hospital
[name]
Moseley
Birmingham
[name]

Heart of England NHS foundation trust

R&D: [name] ([contact] / [name])

Physiotherapy - [name] (head of neuro physiotherapy)

Birmingham Heartlands Hospital

### Inclusion criteria

1) Diagnosis of stroke;

3) Able to walk 10 metres with or without assistance;

4) residual paresis in the lower limb (Fugl-Meyer score < 34);

5) Informed written consent.

### Exclusion criteria

1) Gait speed >0.8 m/s;

2) Patients with a premorbid (retrospective) modified Rankin Scale (mRS)([Rankin 1957](#_ENREF_37)) score>3

3) Gait deficits attributable to non-stroke pathology

4) Visual impairments preventing use of visual cue training (as assessed by Star Cancellation test);

5) a concurrent progressive neurologic disorder, acute coronary syndrome, severe heart failure, confirmed or suspected lower-limb fracture preventing mobilization, and those requiring palliative care;

6) inability to follow a three step command (as assessed by Modified mini-mental status exam).

### Expected duration of participant participation

During the active treatment period, participants will attend the outpatient rehabilitation setting for 1hr., two times weekly for 8 weeks. Participants will then be assessed at follow up 3 months after baseline.

### Removal of participants from therapy or assessments

Participants may permanently discontinue treatment if safety is considered to be at risk e.g. development of comorbidities preventing ability to participate in the treatment, the participant fails to comply with treatment or they withdraw consent. In all of these situations outcome data will continue to be sought at the usual planned time points when the participant and safety permits. Measures will be taken within 5 days following consent and treatment or they will not be included in the dataset at that time point. Given the aims of the study are to determine the numbers of patients who do not complete the allocated treatment, thus dropping out of the study, and determine the reasons for dropping out, withdrawn participants will not be replaced.

### Informed consent

Following the guidance and procedures outlined in the Mental Capacity Act 2005, a senior member of the research team, the research associate, a research nurse from the SRN or a research therapist will approach potentially eligible patients and ask if they are interested in taking part. Once agreed, a meeting will be organised with the patient and if they wish, their family. Prospective participants and their carers will be given a full explanation of the trial by the trial therapist or research associate, who will discuss the study and leave all documentation including the UKCRN publication, ‘Understanding Clinical Trials’ (http://www.ukcrn.org.uk/index/patients/publications.html). This discussion will include explanation of the treatment options in the trial and the manner of treatment allocation. They will be given a participant information sheet (Appendix 6) to read and sufficient time to decide whether they would like to join the trial. This may take a few days if they wish to discuss with family or friends. **Patients will then be asked to sign the consent form (**Appendix 7**). The guidelines of the Mental Capacity Act 2005 will be followed,** if the patient is judged as incapacitated they will not be invited to participate in the trial as it is unlikely they will be able to follow instructions to perform the VCT. The patient’s General Practitioner will be informed in writing of the patient’s participation in the trial (Appendix 8) with the **patient’s consent**.

Although the initial trial procedures will vary from site to site, it is likely that research nurses from The Stroke Research Network, Primary Care Research Network or the Comprehensive Local Research Networks (CLRN) will assist in these processes.

## TRIAL / STUDY TREATMENT AND REGIMEN

The intervention groups under study are: (1) a specialized locomotor training program that includes use of visual cues (VCT) to improve temporal and spatial walking parameters and practice of turning ability as a rehabilitation modality provided on an outpatient basis and (2) a “usual” treatment package aimed at improving overground walking ability provided at outpatient rehabilitation clinics in the west midlands provided for stroke survivors.

The study is designed as a pilot RCT with the primary outcome being successful recovery of walking. Successful recovery of walking is defined as having achieved a 0.4 m/s gait speed or greater for persons with initial severe gait impairment (< 0.4 m/s), or as having achieved a 0.8 m/s gait speed or greater for persons with initial moderate gait impairment (≥ 0.4 m/s – < 0.8 m/s).

**Baseline assessments completed:** walking speed, time and steps taken for 90deg. Turn, Timed-up and Go, Fugl-Meyer Assessment, Berg Balance Scale, Functional Ambulation Classification, 6 minute walk test.

